## Methods

### Recruitment

This study aims to recruit a minimum of 90 patients of whom 30 will receive SBT (with or with no allogeneic blood), 30 will undergo ABT, and the remaining 30 will have NBT. From our experience of treating patients with tumor, there are likely to be very few patients who receive only SBT. The majority of patients receiving SBT are likely to receive both SBT and ABT in various proportions. SBT and ABT form the 2 experimental arms, whereas patients with NBT form the control cohort. We will compare the number of patients receiving only SBT with those receiving ABT, if the sample sizes are sufficient.

Patients will be selected from specialist outpatient spine clinics or inpatient wards. These patients may be referred from an inpatient medical oncology team for management, especially in the setting of MSD with cord compression resulting in symptoms such as pain or neurology. A thorough examination of clinical history, physical examination, and review of imaging will be done, and appropriate patient management options will be discussed by the attending orthopedic surgeon. During the enrollment period, whenever a spine surgeon has obtained surgical consent for MSTS in patients with MSD, the principal investigator (NK) will be informed either by a telephone call or by text messaging.

The *research assistant* who is on-site at the National University Hospital during office hours or any member of the research team who is available will interview the patient. During this interview, the interviewer will confirm whether the inclusion criteria are fully met. The study will be explained to suitable subjects, including the advantages as well as possible intra- and postoperative risks of the reinfusion of salvaged blood. A copy of the *patient information sheet and consent form* will be provided to the patient, detailing the recruitment procedures, our objectives, hypotheses, and background information, and any queries will be addressed. Subsequently, written informed consent will be obtained from the patient.

Blood transfusion details will be collected from anesthetists immediately after the operation. Depending on the type of blood transfusion done during the surgery, that is, ABT only or SBT with or with no ABT or NBT, the patient will be categorized into the appropriate study cohort. All patients undergoing MSTS will receive tranexamic acid as an intravenous bolus before induction of anesthesia as per the department protocol, with subsequent top-up dosages every 4 hours during MSTS. If excessive blood loss is expected during surgery, such as in a separation surgery, continuous infusion of tranexamic acid is given to the patient.

Postoperatively, all subjects will be followed up individually by their operating surgeons, as per the standard of care at the National University Hospital. No additional patient follow-up sessions by the research team will be required. Clinical data and patient outcomes will be accessed via the computerized patient support system and EPIC system at monthly intervals. All available radiological data and clinical notes from the patients’ follow-up by their treating surgeons or physicians will be reviewed by the research team. This is to determine the postoperative outcomes such as survival and disease progression. The collected data will be analyzed postoperatively at 3, 6, 12, 24, 36, and 48 months. The data collection and follow-up of available records will continue over a period of 4 years postoperatively or until the patient’s demise, whichever occurs first. The collected outcomes of the 2 experimental groups (patients who received SBT with or without ABT) will be compared with those of the control group (patients who received NBT) as well as with the available historical data from the literature.

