## Introduction

### Background

The skeletal system is the third most common site of metastases, and cadaveric studies show that spinal metastases can be found in 30% to 90% of patients who die of cancer [1,2]. Surgery for metastatic spine disease (MSD) is complex, often requiring wide resection and extensive reconstruction leading to significant blood loss [1,2]. Emergency surgical treatment is often indicated for spinal cord compression with actual or impending paralysis or for spinal instability with severe pain that reduces the quality of life and mobility [3].

Typical blood loss in a patient undergoing tumor decompression and instrumentation in the thoracic and lumbar spine is about 1500 mL, and this requires an average of 3 units of packed red blood cells [4,5]. This blood loss is currently replenished by allogeneic blood transfusion (ABT) across the world, placing a significant burden on the already limited blood bank resources [6,7]. On the contrary, there is increasing evidence of the deleterious effects of ABT. Many studies have shown an increased incidence of postoperative infections [8] and promotion of tumor growth [8,9], which is thought to occur secondary to immunosuppression and other transfusion reactions.

Despite evidence describing multiple postoperative complications related to ABT [10,11], it remains to be the mainstay of blood replenishment in patients with heavy intraoperative blood loss [12]. These are immune-mediated complications and commonly affect the lungs (eg, transfusion-related acute lung injury) [13,14], wound healing [15-17], and survival duration [11,16]. This has prompted efforts to decrease reliance on ABT and to increase the utilization of alternatives, such as autologous predonation or intraoperative cell salvage (IOCS). Autologous predonation may not always be possible in metastatic spine tumor surgery (MSTS) because of suboptimal patient status, medical comorbidities, and in cases where emergency surgery is indicated.

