### Hypothesis

The working hypotheses of this study are as follows:

Reinfusion of IOCS-LDF–processed blood of patients undergoing MSTS does not increase the risk of disease progression, in terms of tumor progression (increase in size of existing metastatic lesions with or without the appearance of new metastasis) and OS.Patients receiving IOCS-LDF blood transfusion require less ABT.Patients receiving IOCS-LDF blood transfusion will experience fewer overall complications and shorter length of stay than patients receiving ABT.

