### Broader Implications

Through the reporting of our analysis, this study will help reduce the use of ABT, reduce the burden on blood banks, and improve the overall blood management of patients with MSTS. This improvement in blood management will prevail even with the improvement of surgical techniques in the management of MSTS, that is, introduction of minimally invasive surgery techniques and the regular use of navigation. This is because the 2 techniques mentioned earlier will reduce blood loss during the steps of spinal instrumentation but are unlikely to have any effect on blood loss while performing decompression. Decompression and separation surgery presently still form a major component of MSTS and will continue to do so, resulting in significant bleeding that requires replenishment potentially in the form of SBT.

In this protocol, we have proposed a prospective observational nonrandomized study design as the ethical appropriateness of blinding or randomizing these patients is a key concern in our region and country. Blinding or randomization of patients with MSD could be deemed unethical, especially among patients who may not agree to receive SBT or ABT as this will limit the blood transfusion type applicable for them. This could be attributed to the current lack of clinical evidence that SBT does not lead to disease progression or shortened survival among patients undergoing MSTS who receive SBT. With this research proposal, we aim to highlight the safety profile of SBT, together with a design protocol applicable for use in patients with MSD. Future research, such as propensity-matched studies, can be done to further validate the outcomes from our current protocol.

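### The conditional SBT-only versus ABT comparison selects salvage patients on a study outcome (not needing ABT), so it is likely biased towards salvage for outcomes that depend on blood loss

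*Protocol article*

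**What the plan says.** The Recruitment section plans 30 patients in each of three cohorts: SBT with or without allogeneic blood, ABT, and no transfusion. It expects that "there are likely to be very few patients who receive only SBT" and that "The majority of patients receiving SBT are likely to receive both SBT and ABT in various proportions". It then adds the comparison at issue: "We will compare the number of patients receiving only SBT with those receiving ABT, if the sample sizes are sufficient".

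The same section explains how patients enter a cohort. Transfusion details are collected right after the operation, and patients are classified accordingly: "Depending on the type of blood transfusion done during the surgery". The Broader Implications section confirms the design: "we have proposed a prospective observational nonrandomized study design".

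Need for ABT is an outcome in its own right. It appears under Secondary Objectives, in the Hypothesis section ("Patients receiving IOCS-LDF blood transfusion require less ABT") and under Analysis of Primary Outcome Measures. The Hypothesis section also predicts fewer complications and a shorter stay with salvage than with ABT.

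The Statistical Analysis section plans a multivariate Cox model for overall survival and a multivariate subdistribution hazard model for tumor progression. Both concern type of transfusion, and the cumulative incidence curves are drawn for the three transfusion groups. Blood loss is not named as a covariate. No adjusted model is described for complications or length of stay.

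**The concern.** The two sides of the comparison are filtered in opposite directions by something that happens during or after surgery. A salvage patient who goes on to need allogeneic blood leaves the SBT-only group, whereas a patient without salvage must need allogeneic blood to enter the ABT group. The Background section ties ABT to heavy intraoperative loss, so this filter plausibly leaves lighter bleeders in the SBT-only group. The documents do not say so directly; it follows from the definitions.

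If lighter bleeding goes with smaller operations, fewer complications and earlier discharge, the contrast would credit salvage with those advantages. It is also the only contrast in the article that separates salvage from ABT, since the SBT cohort as a whole is expected to be mostly mixed. A favourable result could therefore be given more weight than it deserves.

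**Working it through.** The plan gives no effect size, event rate or expected number for this subgroup, so there is no figure to reproduce. The check asks how far apart the two groups would be if salvage had no effect on outcome.

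**Input from the documents.** "Typical blood loss in a patient undergoing tumor decompression and instrumentation in the thoracic and lumbar spine is about 1500 mL" (Background). This is used as the mean loss.

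**Assumptions not in the documents.** Blood loss L is lognormal with log-SD 0.6. Salvage is reinfused above 300 mL. ABT is given when net loss exceeds 1000 mL (a modelling device, not a clinical rule). Consent to salvage is independent of blood loss.

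**Step 1: blood loss if salvage returns nothing useful.** The log-mean is ln 1500 − 0.6²/2 = 7.313 − 0.180 = 7.133.

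- ABT cohort, L > 1000: z = (6.908 − 7.133)/0.6 = −0.376, so P = 0.646. Mean loss = 1500 × Φ(0.976)/0.646 = 1500 × 0.835/0.646 ≈ 1940 mL.
- SBT-only, 300 < L ≤ 1000: the lower z is (5.704 − 7.133)/0.6 = −2.382, so P = 0.3535 − 0.0086 = 0.345. Mean loss = 1500 × [Φ(−0.976) − Φ(−2.982)]/0.345 = 1500 × 0.163/0.345 ≈ 710 mL.
- SBT-only share of SBT patients: 0.345/0.991 ≈ 35%, about 10 of 30. This is more than the very few that the article expects.

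**Step 2: complications that depend on blood loss only.** Risk = 1/(1 + exp(1.1 − ln(OR) × z)), where z is standardized log loss. This is 25% at the median. It is averaged over each group's range of z. The last two columns sum the binomial probabilities of all tables with 10 SBT-only and 30 ABT patients. Significance is by two-sided Fisher test at 5%.

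| OR per SD of log loss | Risk, SBT-only | Risk, ABT | Crude result points to salvage | Significant for salvage |
|---|---|---|---|---|
| 1.0 | 25% | 25% | 47% | 1% |
| 1.5 | 18% | 30% | 76% | 6% |
| 2.0 | 15% | 34% | 89% | 14% |
| 3.0 | 11% | 39% | 97% | 32% |

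With only 5 SBT-only patients and OR 2, the result still points to salvage in 84% of studies but is significant in about 1%.

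**Step 3: salvage returns blood but does not change outcome.** If a fraction f of the loss is returned, SBT-only patients are those with loss up to 1000/(1 − f).

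- f = 40%, salvage reinfused above 500 mL (losses of 500 to 1667 mL): mean loss 1050 against 1940 mL. Risks are 22% against 30% at OR 1.5, and 21% against 34% at OR 2.
- f = 50%, salvage reinfused only above 1000 mL (losses of 1000 to 2000 mL): mean loss about 1420 against 1940 mL. Risks are 26% against 30% at OR 1.5, and 28% against 34% at OR 2.

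A wider grid has salvage reinfused only above the trigger, with log-SD 0.4 to 0.6, trigger 600 to 1000 mL and 20 to 40% returned. The blood-loss gap runs from about 365 to 951 mL and never closes.

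**Step 4: grouping by consent.** With the Step 1 assumptions and OR 2, grouping by consent to salvage gives simulated risks of 26.8% and 26.9%. The spurious difference disappears because consent is fixed before surgery and, in the model, is unrelated to blood loss.

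**The case against.** The strongest reply is that this is one conditional sentence under Recruitment, in a condensed article, about a subgroup that the authors themselves expect to be tiny. The main plan analyzes the whole SBT cohort and adjusts overall survival and progression for confounders. A covariate list, an endpoint or a minimum size for a side comparison may well sit in a fuller document. Taken literally, the sentence compares head counts, and a head count cannot favour salvage on any outcome. Running a comparison only when the groups are large enough depends on numbers, not on results, so it neither biases the estimate nor inflates the type I error.

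Most of this stands. The missing endpoint and threshold alone would be missing detail, and the condition on size is not the source of bias. What does not fall away is the selection. It is built into the definitions of the two groups, and the adjusted models described cover only survival and progression, not complications or length of stay.

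A reader might infer that the comparison would favour salvage in any event, even if salvage did nothing. The documents do not support that. They give no figure linking blood loss to outcome, and with no such link the bias is nil. If salvage is reinfused only above the ABT trigger and returns nothing, there are no SBT-only patients at all. An effect with inert salvage appears only if salvaged blood is also given to patients below the trigger, as in Step 1. Nor do the documents present this comparison as the study's main safety evidence.

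**Conclusion.** The concern holds in a conditional form. The SBT-only group is selected on a post-treatment event that is also a study outcome, and its comparator is defined by the opposite event. As an outcome comparison it is likely biased towards salvage where blood loss is prognostic and not adequately adjusted for. Complications and length of stay are most exposed.

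The size cannot be fixed from the documents. With salvage having no effect on complications, the gap in risk ranged from zero (blood loss not prognostic), through 3 to 4 percentage points (OR 1.5, salvage reinfused only above 1000 mL with half returned), to 28 points (OR 3, inert salvage). All of this rests on the assumed blood-loss distribution, trigger, returned fraction and prognostic strength. With the very small numbers that the article expects, a significant result would be rare, so the main risk is a favourable-looking estimate rather than a false positive test.

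**What to change.** Replace the sentence with a statement that SBT-only patients will be reported descriptively within the SBT cohort (number, blood loss, volume reinfused), and that no safety or efficacy conclusion will be drawn from that subset.

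Base SBT-versus-ABT inference on the whole SBT cohort, with or without ABT, adjusted for blood loss and type of surgery. Include complications and length of stay in this adjustment. Ideally add a supporting comparison by consent to receive SBT, which is the split described in the Abstract's Objective and is fixed before surgery. The Ethical Considerations section reads as if every recruit consents to SBT, so the sponsor should first confirm that consent status varies and was recorded.

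The cost is a sentence or two of wording and some reanalysis, with no new patients. The sponsor gives up a potentially favourable subgroup result. The whole SBT cohort is still grouped by blood received, so some confounding will remain after adjustment. Patients who consent may also differ from those who decline in ways that the model above does not represent.

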#### Secondary Objectives

The secondary objectives of the study are to investigate whether reinfusion of IOCS-LDF–processed blood can reduce ABT rates in patients undergoing MSTS. We will also compare the length of stay and overall complication rate of patients who receive salvaged blood and those who receive ABT or no blood transfusion (NBT).

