## Discussion

### Study Findings

This is the largest prospective clinical study on the use of IOCS in MSTS from a variety of primary malignancies. It will provide significant clinical evidence regarding the safety and applicability of IOCS in MSTS. The clinical safety of the use of IOCS has been established in oncological surgical procedures involving gastrointestinal [40], gynecological [41-43], hepatobiliary [40,44-46,55-57], and urological [47-54,58-62] specialties (Multimedia Appendix 1). However, the use of IOCS has neither been studied nor practiced regularly in metastatic musculoskeletal tumor surgeries (MMTSs). This may be because of the skepticism among surgeons about the safety of SBT in MMTSs, despite the presence of substantial supporting evidence in other surgical specialties in the field of oncology [40-54,63,64]. Amidst all the apprehension regarding IOCS, a retrospective comparative review has shown that SBT indeed reduces the need for postoperative ABT [69]. More recently, the use of SBT has been studied prospectively, demonstrating its safety for IOCS in MSTS [70]. Nonetheless, these studies did not have a comparative arm and had a small sample size.

This prospective clinical study is founded on substantiating evidence that salvaged blood is free from viable tumor cells, proven in our earlier methodical basic sciences approach [32,38]. We aim to study the OS, as well as tumor progression in MSTS patients through analysis of their various outcome measures. The results from this approach will help debunk the prevailing myth that IOCS contributes to disease progression either in the form of new metastasis or in the form of an increase in the size of the index lesion.

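### Cohorts follow intraoperative transfusion only, so the 'no blood transfusion' controls may include patients given allogeneic blood on the ward, and no time window is set for the ABT outcome

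*Protocol article*

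**What the plan says.** Under Recruitment, the protocol article names one source and one time point for transfusion data: "Blood transfusion details will be collected from anesthetists immediately after the operation". The next sentence gives the allocation rule: "Depending on the type of blood transfusion done during the surgery, that is, ABT only or SBT with or with no ABT or NBT". The three resulting cohorts have these roles: "SBT and ABT form the 2 experimental arms, whereas patients with NBT form the control cohort". The minimum size is 30 per cohort, and the salvage cohort is broad: "This study aims to recruit a minimum of 90 patients of whom 30 will receive SBT (with or with no allogeneic blood"). A narrower comparison is conditional: "We will compare the number of patients receiving only SBT with those receiving ABT, if the sample sizes are sufficient".

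The same section describes a monthly review of electronic records after surgery. Its stated purpose is: "This is to determine the postoperative outcomes such as survival and disease progression". It says nothing about updating transfusion status.

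Statistical Analysis then uses the three-level transfusion type as the exposure for tumor progression, and transfusion type as the exposure for overall survival. Secondary Objectives asks whether reinfusion "can reduce ABT rates in patients undergoing MSTS". Analysis of Primary Outcome Measures compares the proportion transfused and the amount of ABT, without saying over what period either is counted.

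**The concern.** The label and the rule differ. The control cohort is called no blood transfusion, but the rule only ensures that none was given in theatre. The Introduction attributes infection and tumor growth after ABT to immunosuppression, and nothing in that argument is limited to units given during the operation. A control patient transfused on the ward therefore has the exposure the control group is meant to lack.

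Two results are at stake. First, the leading hypothesis is that salvaged blood does not increase the risk of progression or death. If ABT is harmful, as the Introduction argues, ward-transfused controls worsen the control group's outcomes, and SBT looks safer by comparison. Second, the ABT-sparing hypothesis needs a full count of ABT. If only theatre units are counted, salvage that postponed ABT to the ward would be scored as having avoided it. The authors regard later ABT as relevant: Study Findings cites a retrospective review as showing that "SBT indeed reduces the need for postoperative ABT".

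**Working it through.** There is no stated figure to reproduce: the minimum of 90 comes without an effect size, event rate or power. The check is therefore a reading of the text followed by an illustration.

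**Where ward ABT could enter the plan**

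- NBT cohort: affected. The rule looks only at the operation, so later ABT leaves the label unchanged.
- Salvage-only comparison: affected for the same reason, but it is conditional and the authors expect very few such patients.
- Main SBT cohort: not affected. It is defined with or without ABT, so ward ABT cannot move a patient in or out.
- ABT-only cohort: not affected. These patients had ABT in theatre by definition.
- Salvage exposure itself: fully captured, since salvage is intraoperative.
- ABT outcome: open. No window is stated, and the only transfusion data source described is the anesthetists' report at the end of surgery.

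**Illustration for the ABT versus NBT contrast**

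Inputs from the document: 30 patients per cohort (the minimum) and a two-sided 5% level. Assumptions: a share p of the NBT cohort receives ward ABT, carries the full ABT hazard and otherwise resembles the rest of NBT; the true hazard ratio (HR) for ABT against no ABT is 2.0 or 1.5; there are 60 events, meaning every patient in two cohorts of 30 has one.

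- Mislabelled controls = 30 × p.
- Apparent HR ≈ HR / (1 − p + p × HR). For p = 0.10 and HR = 2.0: 2.0 / (0.90 + 0.20) = 1.82.
- Power ≈ Φ(√(60/4) × ln(apparent HR) − 1.96). For HR = 2.0 and p = 0: Φ(3.873 × 0.693 − 1.96) = Φ(0.725) = 0.766.

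| p (assumed) | Mislabelled of 30 | Apparent HR, true 2.0 | Power | Apparent HR, true 1.5 | Power |
|---|---|---|---|---|---|
| 0 | 0 | 2.00 | 0.766 | 1.50 | 0.348 |
| 0.10 | 3 | 1.82 | 0.639 | 1.43 | 0.281 |
| 0.20 | 6 | 1.67 | 0.507 | 1.36 | 0.224 |
| 0.30 | 9 | 1.54 | 0.385 | 1.30 | 0.176 |
| 0.40 | 12 | 1.43 | 0.281 | 1.25 | 0.137 |

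**The safety contrast, SBT versus NBT**

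Under the same assumptions the control hazard is multiplied by 1 − p + p × HR, so the SBT versus NBT hazard ratio is divided by that factor. With an ABT hazard ratio of 2.0, the divisor is 1.1 at p = 0.10 and 1.3 at p = 0.30. The shift favors the hypothesis of no added risk.

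**The ABT outcome**

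Counting theatre units only, the ABT rate is 100% in the ABT-only cohort and 0% in NBT by construction. Adding ward units leaves the first at 100%, but can raise the rate in NBT and among salvage-only patients, and can raise total units in any cohort. Total units is therefore where most of the missing information lies.

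**The case against.** The strongest reply is that grouping at the end of surgery is sound. It gives a clean time zero, and ward ABT is a later event driven partly by bleeding and complications and partly by salvage itself. The exposure under test is salvaged blood, and the theatre record captures all of it. This stands, and it is why the groups should not be redrawn.

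A second reply is that the anesthetists' report serves cohort assignment and does not define the ABT outcome. The monthly review covers all available clinical notes, and its list of outcomes is open-ended, so ward units may well be counted. This stands in part. A reader might infer that postoperative ABT goes unrecorded or is excluded; the article does not say so. Nor does the review cited in Study Findings, which describes another study, define this one's endpoint. An article may leave an endpoint window to a fuller document. The exposure rule, however, is stated outright, and no transfusion data source beyond the theatre report is described, so someone following the text could properly omit ward units.

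A third reply is that the illustration rests on an unsourced ward rate and mainly concerns ABT versus NBT. That is right. Ward-transfused patients may also be sicker than other controls, so neither the size nor, strictly, the direction of the distortion is assured.

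**Conclusion.** The point holds in a limited form. By its stated rule, the plan defines its control cohort by intraoperative transfusion while labelling it as untransfused, and it leaves the period for counting ABT open. The NBT cohort and the conditional salvage-only comparison can therefore contain ABT-exposed patients, and the ABT-sparing comparison can miss postoperative units.

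A reader might infer that the whole exposure classification is compromised. It is not: salvage exposure and main SBT membership are unaffected. A reader might also take 3 to 9 mislabelled controls, or an attenuation from 2.0 to between 1.82 and 1.54, as an estimate. These are consequences of an assumed 10% to 30% ward rate, a full ABT effect in those patients and otherwise comparable controls. The actual effect cannot be determined from the document. The change is still worth making, because it is cheap and the likely distortion, if ABT is harmful, favors the conclusions the study hopes to reach.

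**What to change.** 1. Keep the end-of-surgery groups, but name them as intraoperative exposure throughout, for example 'no intraoperative transfusion' for the control cohort.
2. Extract all allogeneic units from start of surgery to discharge from the electronic records already reviewed monthly. In Analysis of Primary Outcome Measures, use that total (any ABT, and number of units) as the ABT outcome.
3. For overall survival and progression, add a sensitivity analysis with postoperative ABT as a time-dependent covariate, or a landmark analysis from the end of a fixed postoperative window. A landmark needs the same day for every patient, so discharge itself will not serve. For progression, the landmark form fits the planned subdistribution model more easily, because a time-dependent covariate is hard to define for patients kept in the risk set after death.

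Do not redefine the primary groups by postoperative ABT. That would make membership depend on events after exposure and on the ABT outcome itself: a group selected for no ABT within the window has none in it by construction. It would also move controls with complicated recoveries into the ABT group, biasing the complication and length-of-stay comparisons against ABT.

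The cost is a little extra chart extraction and analysis, with no new visits or patients. The apparent ABT saving may turn out smaller.

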**Objective:**

This study aims to analyze safety of IOCS-leukocyte depletion filter (LDF)–processed blood transfusion for patients undergoing MSTS by assessing clinical outcomes—disease progression: tumor progression and overall survival. This study evaluates whether reinfusion of IOCS-LDF–processed blood reduces ABT rates in patients undergoing MSTS by sorting patients undergoing MSTS who require ABT into patients who consent to receive or not receive SBT.

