#### Analysis of Primary Outcome Measures

We intend to compare the proportion of patients with MSTS requiring blood transfusion and the amount of ABT required. The primary analysis will be based on the intention-to-treat principle. A Fisher exact test will be used to compare the 2 arms. The exact 95% CI will also be calculated for the difference in the ABT rate between the 2 arms.

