### Ethical Considerations

The domain-specific review board of the National Healthcare Group, Singapore (reference numbers: 2014/00065 and 2022/00866), has granted ethical approval for this study. Written informed consent regarding participation in this research study and receiving SBT will be obtained from each patient before the patient is recruited for the study. Data have been anonymized and deidentified. No compensation was provided to patients for this study.

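### Cohorts are defined by the blood given in theatre, so the ABT-rate comparison between the SBT and ABT arms cannot test whether cell salvage spares ABT, and the intention-to-treat label does not fit

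*Protocol article*

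**What the plan says.** **How cohorts are formed.** In Recruitment, "Blood transfusion details will be collected from anesthetists immediately after the operation", and each patient is then placed in a cohort: "Depending on the type of blood transfusion done during the surgery, that is, ABT only or SBT with or with no ABT or NBT". The target is to "recruit a minimum of 90 patients of whom 30 will receive SBT (with or with no allogeneic blood), 30 will undergo ABT", with 30 untransfused patients (NBT) as control. The same section names SBT and ABT as the two experimental arms. It expects hardly any SBT patients to avoid allogeneic blood altogether: "The majority of patients receiving SBT are likely to receive both SBT and ABT in various proportions".

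**What is compared.** Analysis of Primary Outcome Measures names two quantities, the proportion needing transfusion and the amount of ABT. It specifies a Fisher exact test between the two arms and adds: "The exact 95% CI will also be calculated for the difference in the ABT rate between the 2 arms". On the analysis set it says: "The primary analysis will be based on the intention-to-treat principle". Statistical Analysis sets two-sided tests at 5%.

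**Consent and assignment.** The abstract's Objective describes another rule for the ABT question. It takes patients who need ABT and sorts them "into patients who consent to receive or not receive SBT". Ethical Considerations says: "Written informed consent regarding participation in this research study and receiving SBT will be obtained from each patient before the patient is recruited". Broader Implications calls the study observational and nonrandomized and refers to patients who might refuse SBT or ABT.

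**The concern.** The ABT question asks whether offering cell salvage lowers the chance or amount of allogeneic transfusion. To answer it, the groups must be fixed without reference to whether ABT was given. Here ABT is used first to build the groups and then as the outcome compared between them.

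A patient with salvage set up but nothing reinfused counts as ABT if given allogeneic blood and as NBT if not. A patient without salvage who needs no blood also leaves the comparison. What remains in the ABT arm is, by construction, only patients who had ABT.

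The Hypothesis section says SBT patients will require less ABT, and Broader Implications says the study will help reduce ABT use. The planned test could be read as support for both statements while carrying no information on either. The intention-to-treat label would make the result look protected against exactly this selection.

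**Working it through.** The article gives no ABT rate, effect size or power for this comparison, so there is no stated figure to reproduce beyond the 30 per cohort. The check is of structure.

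**1. What the cohort rule fixes.**

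| Cohort | Any intraoperative transfusion | Intraoperative ABT |
|---|---|---|
| ABT only | 100% | 100% |
| SBT with or without ABT | 100% | (30 − k)/30 |
| NBT | 0% | 0% |

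Here k is the number of SBT patients who had no ABT. The proportion transfused is therefore fixed in every cohort. The ABT-rate difference (ABT minus SBT) is 30/30 − (30 − k)/30 = k/30, which is never below zero.

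**2. The P value as a function of k.** With 30/30 against (30 − k)/30, all k patients without ABT lie in one arm. The mirror-image table is equally probable, so the two-sided Fisher P = 2 × C(30,k)/C(60,k), capped at 1.

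- k=3: P=.237
- k=4: P=.112
- k=5: 2 × 142,506/5,461,512 = .052
- k=6: 2 × 593,775/50,063,860 = .024

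At these arm sizes, crossing 5% is simply a count reaching six.

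**3. How likely that count is.** The article gives no number of SBT-only patients, so the share q is an assumption. P(k ≥ 6) from a binomial with n=30:

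- q=5%: 0.3%
- q=10%: 7%
- q=20%: 57%
- q=30%: 92%

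If SBT-only patients are as rare as the article expects, a null is the likely result. It would say only that few SBT patients avoided ABT.

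**4. What happens if salvage does nothing.** Assumptions, none from the article: 90 patients; salvage intended in half, at random; 80% of those reinfused; allogeneic need p independent of salvage; 4,000 simulated trials per p. The SBT arm then has ABT rate p and the ABT arm 100%, so the expected difference is 1 − p although the true effect is zero.

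| p | Cohorts by blood given: mean difference | P<.05 | Groups by preoperative intent: mean difference | P<.05 |
|---|---|---|---|---|
| 40% | 60 points | 100% | about 0 | 4% |
| 60% | 40 points | over 99% | about 0 | 3% |
| 80% | 20 points | 92% | about 0 | 4% |

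In these runs the SBT-only share is 1 − p, that is 20% to 60%, more than the article foresees. The arms are also larger than 30 (at p=80%, about 90 × 0.5 × 0.8 = 36 SBT and 54 × 0.8 = 43 ABT), so fewer than six SBT-only patients suffice. The table shows that the comparison cannot recognise a useless intervention. It does not forecast this study's P value.

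**5. Amount of ABT.** The rule does not fix this. But the ABT-only cohort is selected to have more than zero units while the SBT cohort may include zeros, so the contrast is distorted by selection.

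**6. Intention-to-treat.** Recruitment groups by treatment received, which is an as-treated grouping, and Broader Implications confirms that nothing is randomized. The abstract's consent rule could supply an intention, but it is restricted to patients who need ABT, which again conditions on the outcome. Read literally, Ethical Considerations has every recruit consent to SBT, leaving nobody who declined. Broader Implications points the other way.

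**The case against.** The strongest reply is that the point is narrower than it first appears, and much of that stands.

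- **A reader might infer that the result must always favour SBT.** It need not. If every SBT patient also has ABT, the difference is zero, and with five or fewer SBT-only patients of 30 the test does not reach 5%. The definition rules out only a result favouring ABT.
- **A reader might infer that postoperative ABT is excluded.** The cohort rule uses blood given during surgery, but the outcome has no stated time window, and the research team does review the electronic record. Postoperative ABT is unaddressed, not left out.
- **A reader might try to sign the bias within the SBT arm.** Suppose 40 set-ups: 24 with SBT and ABT, 6 SBT-only, 10 ABT-only after poor salvage. The plan reports 24/30 = 80%, against 34/40 = 85% by intention. Add three set-ups that end with no transfusion and the intention figure becomes 34/43 = 79%. The direction depends on counts the article does not give.
- **A reader might say an intention-type analysis is impossible here.** The abstract's consent rule suggests one could be built, but not on the cohorts as the Recruitment section defines them.
- **ABT reduction is a secondary objective.** Primary and Secondary Objectives make progression and OS primary; only the analysis heading places ABT first. The defect leaves the progression and OS comparisons untouched.

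None of this rescues the ABT-rate test. Nor is it a detail an analysis plan could supply: the article states the cohort rule, the test, the interval and the analysis set, and an analysis plan could make them compatible only by overriding one of them.

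**Conclusion.** The point holds in this form: the ABT-rate comparison between the SBT and ABT arms is uninformative about whether cell salvage reduces ABT, whatever its P value. The ABT-arm rate is 100% by definition, the difference is k/30 and cannot be negative, and at 30 v 30 the result turns on whether five (P=.052) or six (P=.024) patients had SBT alone. These statements follow from the article's own definitions and its target of 30 per arm. The chances of significance and the simulated differences rest on the assumptions stated with them. The amount of ABT is distorted by selection but not predetermined. The intention-to-treat label does not fit as-treated cohorts in a nonrandomized study, and the statements on who consents to SBT conflict. The ABT comparison should not be reported as planned.

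**What to change.** 1. Reconcile the abstract's Objective, Recruitment, Ethical Considerations and Broader Implications on whether patients are sorted by consent to SBT and whether all of them consent to it.
2. For the ABT question, if consent forms and theatre records show it, define two groups by what was fixed before incision: salvage accepted or set up, versus not. Keep every patient in the denominator, including those who received no blood. Compare any ABT and ABT units over a stated window. Adjust for baseline confounders such as expected blood loss and primary tumor, since the choice to set up salvage may follow expected bleeding.
3. If no such preoperative contrast can be recovered, drop the ABT-rate test, its interval and the intention-to-treat label, and report ABT use by cohort descriptively. This fallback is sound whatever the records show.
4. Keep the blood-received cohorts for progression and OS, labelled as-treated.

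**Cost.** Step 2 needs a review of consent and theatre records. The article does not say that salvage set-up was recorded, and recruitment has ended, so this may fail. If every recruit did consent to SBT, only set-up versus no set-up remains as a contrast. Arm sizes would probably be unequal. Step 3 needs only a change of wording, but leaves a weaker claim about ABT reduction.
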